[**13.** **Tables** 11](#_Toc141888147)

[a. Baseline characteristics 11](#_Toc141888148)

[b. Primary outcome 12](#_Toc141888149)

[c. Safety outcomes 12](#_Toc141888150)

[d. Secondary outcomes 13](#_Toc141888151)

[**14.** **Figures** 14](#_Toc141888152)

[a. Flowchart of participants 14](#_Toc141888153)

[**15.** **References** 14](#_Toc141888154)

1. **List of abbreviations**

- BTA Botulinum toxin A
- CPP Chronic pelvic pain
- EQ-5D Quality of life questionnaire
- HADS Hospital Anxiety and Depression Scale
- MAPle Multiple Array Probe Leiden
- PCS Pain Catastrophizing Scale
- PFDI-20 Pelvic Floor Distress Inventory 20
- PFIQ-7 Pelvic Floor Impact Questionnaire 7
- PGI-I Patient Global Impression of Improvement
- PISQ-IR Pelvic Organ Prolapse/Incontinence Sexual Questionnaire, IUGA-Revised
- RCT Randomized controlled trial
- QoL Quality of Life
- VAS Visual Analogue Scale

1. **Introduction**
   1. Background

Chronic pelvic pain is common, affecting 15% of women aged 18-50^1^. Pelvic floor muscle spasms resulting in chronic pelvic pain may occur as a primary event or secondary to a physical, psychological or pathological factor. First-line treatment consists of pelvic floor physiotherapy. When first-line treatment fails, more invasive interventions can be done. One previously published intervention is injection with botulinum toxin A (BTA) in the pelvic floor muscles. It produces a localized, partial, and reversible chemical denervation of the muscle which results in localized muscle weakness or paralysis. There is some evidence that injection of BTA in the hypertonic pelvic floor muscles decreases pelvic pain in patients with therapy resistant chronic pelvic pain; however this is not investigated in a randomized controlled trial.

- 1. Objective

The primary objective of this randomized, double-blind, placebo controlled trial was to compare the effect of BTA injections vs. placebo injections on pelvic pain in women with chronic pelvic pain.

1. **Endpoints**
   1. Primary endpoints

Decrease of chronic pelvic pain, measured by a decrease in visual analog scale score (VAS score 0-10) with 33% and a patient global impression of improvement score (PGI-I) of 1 or 2 (better or much better) at 26 weeks after injection.

- 1. Secondary endpoints
     1. Subjective outcomes (patient reported outcomes)
- pelvic floor distress inventory (PFDI-20)^2^
- pelvic floor impact questionnaire (PFIQ-7)^2^
- quality of life (EQ-5D)^3^
- painDETECT^4^
- pain catastrophizing scale (PCS)^5^
- hospital anxiety and depression scale (HADS)^6^
- sexual function (PISQ-IR)^7^
- Visual analog scale (VAS) score ^8^
  - 1. Anatomical outcomes
- Pelvic floor hypertonicity measured by the MAPLe device
  - 1. Other outcomes
- A cost-effectiveness analysis will be performed in case of a significant improved VAS score and quality of life.
  1. One year follow-up

To evaluate the safety and efficacy of a BTA injection one year after BTA injection.

- 1. Open label extension study

To evaluate the safety of BTA injection 26 weeks after the placebo injection in participants who did not reach the primary endpoint.

1. **Study methods**
   1. Study design

Double-blinded randomized placebo-controlled trial.

- 1. Study population

Patients over 16 years with >6 months of chronic pelvic pain with pelvic floor muscle hypertonicity refractory to first-line pelvic floor physiotherapy, and in whom no anatomical cause was found.

* Definition by the International Continence Society: Chronic pelvic pain is characterized by persistent pain lasting longer than 6 months or recurrent episodes of abdominal/pelvic pain, hypersensitivity or discomfort often associated with elimination changes, and sexual dysfunction often in the absence of organic etiology^9^.

- 1. Inclusion criteria
- Female, >16 years
- Chronic pelvic pain according to the ICS with or without dyspareunia
- Vaginal examination with one finger possible
- Pelvic floor hypertonicity measured by physical examination by registered pelvic floor physiotherapist and MAPLe
- Previous physical therapy with registered physical therapist was unsuccessful
- Good understanding of Dutch language
- Willing to provide informed consent
  1. Exclusion criteria
- (wish for) Pregnancy/lactation during study period
- Previous pelvic floor BTA treatment
- Known hypersensitivity to BTA
- History of neuromuscular or bleeding disorders
  1. Treatment of subjects

The pelvic floor muscles will be injected with either 100 IU BTA or placebo.

- 1. Study procedures

The subjects will undergo the following procedures after signing informed consent:

- Physical examination by a gynecologist and a physical therapist
- MAPLe measurement by a physical therapist
- The patient preference questionnaire will be filled in
- The validated questionnaires will be filled in at baseline, 4, 8, 12 and 26 weeks after injection
- Injection of study medication or placebo in pelvic floor muscles
- Standardized physical therapy by an experienced registered pelvic floor physical therapist during the study period
- Deblinding of subjects who did not meet the primary endpoint and offer them a second injection with BTA.
- As part of the Open-label Extension Study, subject will fill in validated questionnaires at 4, 8, 12 and 26 weeks after BTA injection.
- One year follow-up questionnaires will be filled in after the primary BTA/placebo injection or one year after the BTA injection in case of the Open-label Extension Study.
  1. Study medication and preparation

The investigational medicinal product (IMP) will either be Botulinum Toxin Type A 100IU or 0.9% NaCl (placebo).

The BTA and placebo will be supplied from site stock, where it is stored according to Good Distribution Practice (GDP ), recommended respectively in Dutch hospital pharmacies and outpatient clinics. The drugs will become investigational medicinal products only when they are made ready for administration.

The independent health professional, not involved in the study or treatment of the patient, will prepare the syringe with the investigational medicinal product under aseptic conditions just before administration. The independent health professional will dissolve 100IU BTA in 6cc 0.9% NaCl in a syringe or only 6cc 0.9% NaCl in a syringe, depending on the treatment arm. This process will always be verified by a second, independent person (controller) to assure that the process is done correctly.

- 1. Randomization procedure and blinding

Participants were randomly allocated to BTA injection or placebo injection in a 1:1 ratio. The 94 sealed opaque envelopes were randomly divided across the inclusion centres and opened on the day of randomization. The gynaecologist, physical therapist and participant were blinded to the treatment arm. Participants who did not meet the primary endpoint (33% reduction VAS score or PGI-I 1 or 2) were deblinded after 26 weeks. Participants who received placebo injection were offered to participate in our open label extension study and receive BTA injection concurrent with pelvic floor physical therapy.

[figure not shown]

Figure 1. flow-chart RCT

[figure not shown]

Figure 2. flow-chart follow-up studies after ending of RCT: one year follow-up and open-label extension study

- 1. Replacement of individual subjects after withdrawal

If withdrawal occurs before the injection, these patients will be replaced in order to reach the desired statistical power. If withdrawal occurs during the follow-up period, between injection and before the endpoint of 26 weeks, the data will be censored at the last available time-point. Analyses of available data will be performed in the intention to treat group.

1. **Sample-size**

The ANCOVA procedure^10^ showed that to detect a statistical significant 33% difference in pain scores between the intervention group and the control group, a sample size of 94 individuals was required for this trial (47 per group), with 80% power and assuming a two-sided alpha of 0.05.

1. **Analysis considerations**

To evaluate the effect of BTA on the VAS score during follow-up all statistical analysis will be performed according to intention to treat principle.

- 1. Analysis of groups

The intention-to-treat (ITT) population is the as-randomized population. This will consist of all patients who have given consent and have been allocated to one of the two treatments, irrespective of treatment received.

- 1. Covariates and Subgroups

Subgroup analyses are planned to investigate the possible effect on the outcome of treatment of the following possible pre-defined interaction terms:

- Menopausal status (yes vs. no)
- Negative sexual experience (yes vs. no)
- Depression scale at baseline (HADS) (scale 0-21 points)
- Previous operations (Abdominal/pelvic operation vs other)
- Parity (absolute numbers)
- Use of pain opioids (yes vs. no)
- Sexual activity (yes vs. no)

Subgroup analyses will be conducted by adding an interaction term to the model and testing for the statistical significance of this interaction term. We will subsequently examine the likelihood that we have missed any relevant interaction terms through a likelihood ratio test for all baseline characteristics available.

In version 5 of our statistical analysis plan we added one subgroup to our analysis:

- Duration of CPP (<1 year vs. >1 year)

Furthermore, due to our study design (double-blind randomized controlled trial), we determined that covariates did not add value to our analysis.

- 1. Missing data

We will use mixed models for repeated measurements and its ability to handle missing data effectively. Before analyzing our results using mixed models for repeated measurements, the following questions will be answered:

1. Is the occurrence of missing data random, or is there a discernible pattern among these individuals?
2. What is the source of the missing data?
3. Is there any correlation with specific variables?
4. Can we identify a pattern in the missing data?

Based on the answers to these questions, the potential options for the pattern of missing data are as followed: Missing completely at random (MCAR), missing not at random (MNAR), and missing at random (MAR).

In case of additional analyses not performed using mixed models, missing data will be examined and if necessary randomly imputated.

Patients who are lost to follow-up will be censored at the last visit on which all assessments were completed.

- 1. Interim Analyses and Data Monitoring

No interim analyses are planned.

1. **Efficacy analyses**
   1. Timing of final statistical analysis

The statistical analyses of the primary outcome and secondary outcomes (measured 26 weeks after treatment) will be performed after a minimum of 26 weeks have elapsed from the inclusion of the final patient in the study and after data cleaning for these outcomes has been completed.

The statistical analysis of the follow-up study will be performed 26 weeks after inclusion of the final patient and data cleaning for these outcomes has been completed.

- 1. Primary and secondary outcome analysis

The null hypothesis entails that there is no significant difference in decrease of chronic pelvic pain scores 26 weeks after treatment between the intervention group receiving BTA injections and the control group receiving placebo injections among women with chronic pelvic pain.

VAS score Analysis:

- Mixed models for repeated measurements will be used. VAS scores will be compared over time between groups
- Primary endpoint: Percentage difference in VAS score between baseline and 26 weeks post-treatment will be calculated for each group.

PGI-I Analysis:

- Mixed models for repeated measurements will be used.
- PGI-I scores will be analyzed to identify differences between groups over time.
- Primary endpoint: the primary outcome of PGI-I scores being 1 or 2 (presented as median and interquartile (IQ) range) will be compared between groups.

Secondary outcome analysis

Questionnaire Scores:

- The total scores of all questionnaires will be analyzed over time using mixed models for repeated measurements.
- Analysis will involve assessing changes over time between groups MAPLe
- EMG signals will be analysed using mixed models for repeated measurements

The analyses will be performed with IBM SPSS Statistics (version 29, Armonk, New York, United States) and R.

In our version 5 statistical analysis, we found that adjusting for baseline and age did not enhance our analysis, given our study's design as a double-blind randomized controlled trial. Therefore, we removed this adjustment from our statistical analysis plan.

1. **Safety analyses**
   1. Adverse events

Adverse event data will be analysed as allocated (intention-to-treat) and 95% confidence interval will be calculated where possible. We do however not foresee a high number of adverse events and in that case adverse events will be mentioned in a table or the text.

- 1. Deaths, Serious Adverse Events and other significant Adverse events

Death/serious adverse events will be described by treatment group.

1. **Other analyses**

Subgroup analysis mentioned in section 6 is seen as hypothesis generating.

1. **Comparison to study protocol**

The current analysis plan is largely based on the published study protocol^11^. Slight changes were made and these are listed below:

- Not only IBM SPSS Statistics for Windows, Version 26.0. will be used, but also R.
- We will not use Kaplan Meier to estimate the success rates at 26 weeks of follow-up. Instead we will use the mixed models for repeated measurements.

1. **Presentation of study results**
   1. Recruitment

The flow of recruitment of study participants will be presented in the CONSORT flow diagram^12^.

- 1. Protocol violations

All protocol violations will be line-listed by treatment group.

- 1. Baseline characteristics

Baseline characteristics of the total randomized (intention-to-treat) population will be presented following the format of the mock table provided in section 13. Discrete outcomes will be presented using absolute numbers and percentages, while continuous outcomes will be presented as means with standard deviations or medians with interquartile ranges.

- 1. Primary outcome

The primary outcome will be presented for the total population as randomised (intention-to-treat). Data will be presented using absolute numbers with percentages for discrete outcomes. Relative Risk or mean difference will be presented together with 95% confidence interval, and p-value otherwise as appropriate.

- 1. Secondary outcomes

The secondary outcomes will be presented for the total population as randomised (intention-to-treat). Data will be presented using absolute numbers with percentages for discrete outcomes. Relative Risk or mean difference will be presented together with 95% confidence interval, and p-value otherwise as appropriate.

1. **Definition of variables**
   1. Primary outcome

- VAS sore: we will use the painDETECT questionnaire to determine patients VAS score at every time point. We will use the following question out of the painDETECT questionnaire:
  - - - How strong was the pain during the past 4 weeks on average?

We believe that the average pain score over the past 4 weeks provides a more accurate reflection of the current situation than the pain score at the specific moment itself. The latter is influenced by various other factors.

- PGI-I: we will measure our patients interpretation of symptom changes following treatment. A score of 1 or 2 will be considered clinically significant and relevant.
  1. Secondary outcomes
     1. Patient reported outcomes based on questionnaires. Scores of the questionnaires will be calculated in line with the questionnaire instruction.
- pelvic floor distress inventory (PFDI-20): raw outcomes will be transformed into the following results: Pelvic Organ Prolapse Distress Inventory-6 (POPDI-6), Colorectal-Anal distress Inventory 8 (CRAB-8), Urinary distress Inventory 6 (UDI-6) and the PFDI total score
- pelvic floor impact questionnaire (PFIQ-7): raw outcomes will be transformed into the following results: Urinary impact questionnaire (UIQ-7), Colorectal-anal impact questionnaire CRAIQ-7, Pelvic organ prolaps impact questionnaire (POPIQ-7) and the PFQI-7 total score.
- quality of life (EQ-5D)
- painDETECT: raw outcomes will be transformed into a painDETECT total score and will be categorized into negative, unclear and positive.
- pain catastrophizing scale (PCS): raw outcomes will be transformed into a pain catastrophizing total score
- hospital anxiety and depression scale (HADS): raw outcomes will be transformed into: depression score and anxiety score
- the Pelvic Organ Prolapse/Incontinence Sexual Questionnaire, IUGA-Revised (PISQ-IR): raw outcomes will be transformed into the following results:
  - 1. Multiple Array Probe Leiden (MAPLe): this method involves measuring the EMG signals closest to the pelvic floor, allowing us to assess pelvic floor muscle tone at 24 different locations. EMG signals will be recorded during periods of rest, endurance and the maximum voluntary contraction. Measurements are standardized through a protocol. We will specifically focus on the EMG measurements taken during rest. This particular measurement is considered the most reliable, as opposed to the other measurements which are derived as averages of three to ten individual measurements.

1. **Tables**
   1. Baseline characteristics

| **Table 2.** Baseline characteristics by treatment group | | |
| --- | --- | --- |
| **Characteristics** | BTA  (n=x) | Placebo  (n=x) |
| Age, median [IQR], y | Median [IQR] | Median [IQR] |
| Ethnicity: Caucasian (%) | NNN% | NNN% |
| Body mass index (BMI)^a^ , median [IQR] | Median [IQR] | Median [IQR] |
| Parity, No. (%)  - Nulliparous  - Primiparous  - Multiparous | NNN%  NNN%  NNN% | NNN%  NNN%  NNN% |
| Menopausal, No. (%) | NNN% | NNN% |
| Relationship status: in a relationship, No. (%) | NNN%^Ω^ | NNN% |
| Sexually active, No. (%) | NNN% | NNN% |
| History of sexual abuse, No. (%) | NNN% | NNN% |
| Smoking, No. (%) | NNN% | NNN% |
| Surgical history ^b^, No. (%)  - Abdominal surgery  - Laparoscopic surgery  - Prolapse surgery  - Other | NNN%  NNN%  NNN%  NNN% | NNN%  NNN%  NNN%  NNN% |
| Pain score at baseline^c^, mean [SD] | Median [IQR] | Median [IQR] |
| Use of pain medication, No. (%)  - No use of pain medication/ paracetamol  - Non-steroidal anti-inflammatory drugs (NSAIDs)  - Neuropathic pain medication^d^  - Opioids | NNN%  NNN%  NNN%  NNN% | NNN%  NNN%  NNN%  NNN% |
| Other chronic pain syndromes (not CPP)^b,e^, No. (%) | NNN% | NNN% |
| ^a^ Calculated as weight in kilograms divided by height in meters squared  ^b^ Data were collected at the study inclusion visit and were supplemented by study research nurses through medical record review.  ^c^ Average pain score past four weeks, scale 0-10  ^d^ Amitriptyline, gabapentin, pregabalin and nortriptyline.  ^e^ Including: fibromyalgia, piriformis syndrome, irritated bowel syndrome, interstitial cystitis, provoked vulvodynia | | |

- 1. Primary outcome

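### The one-year aim is labelled efficacy, but after week 26 treatment and blinding depend on response, so the data give no unbiased BTA-versus-placebo effect at one year

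*SAP*

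**What the plan says.** Under Endpoints, the one-year follow-up has the aim "To evaluate the safety and efficacy of a BTA injection one year after BTA injection". The item that follows, on the open-label extension, is limited to safety: "To evaluate the safety of BTA injection 26 weeks after the placebo injection in participants who did not reach the primary endpoint". Efficacy is thus claimed for the one-year follow-up and not for the extension.

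Under Study methods, Randomization procedure and blinding: "Participants who did not meet the primary endpoint (33% reduction VAS score or PGI-I 1 or 2) were deblinded after 26 weeks". This covers both arms. The section continues: "Participants who received placebo injection were offered to participate in our open label extension study and receive BTA injection". The Study procedures list puts the offer differently, with no restriction by arm: "Deblinding of subjects who did not meet the primary endpoint and offer them a second injection with BTA".

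The same list sets two time origins for the one-year data: "One year follow-up questionnaires will be filled in after the primary BTA/placebo injection or one year after the BTA injection", the second applying to extension participants.

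Analysis considerations applies intention to treat, as randomised, to all analysis of the BTA effect on VAS during follow-up. Efficacy analyses gives only a time point for analysing the follow-up study. No section names a one-year comparator, endpoint or model, or says how the switch to open-label BTA is handled.

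**The concern.** Up to week 26 the trial is a blinded randomised comparison. After week 26, whether a woman in the placebo arm receives BTA depends on how she fared, and non-responders in either arm learn what they received. An aim of efficacy at one year, with no estimand or analysis attached, leaves the analyst free to choose among several comparisons after the data are seen. None of them estimates the effect of the first BTA injection against placebo without bias, and they err in different directions. A reader of the report could take any of them as evidence for or against lasting efficacy.

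**Working it through.** The SAP gives no figure for the one-year follow-up, so there is none to reproduce. It also gives no baseline pain, SD, placebo response rate or uptake. All numerical inputs below are assumptions, and response is simplified to a 33% fall in VAS, without PGI-I.

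**1. Who contributes what at one year**

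| Group | After week 26 | One-year clock |
|---|---|---|
| BTA, responder | no further injection planned | first injection |
| BTA, non-responder | deblinded; further BTA offered or not, depending on which statement applies | first injection |
| Placebo, responder | no switch described for responders | first injection |
| Placebo, non-responder, declines | deblinded | first injection |
| Placebo, non-responder, accepts | deblinded, open-label BTA | BTA injection |

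If the extension injection is given at week 26, its one-year questionnaire falls at about week 26 + 52 = 78 from the first injection. The extension's own 26-week questionnaire falls at about week 26 + 26 = 52.

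**2. Comparison with placebo women who did not switch, no treatment effect**

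Assumed: baseline mean 7, SD 0 to 1.3; mean fall 1.5; SD of individual deviations 2.3; correlation of week-26 and one-year deviations 0.3 to 0.7; scores bounded at 0 and 10. About 36% then reach the VAS cut-off at week 26 in either arm.

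| Non-responders who switch | Remaining placebo group scores lower than the BTA arm by | One-year responders, remaining placebo vs BTA |
|---|---|---|
| all, baseline SD 1.3 | 0.9-1.8 points | about 49-68% vs 36% |
| all, baseline SD 0 | 0.7-1.6 points | about 48-68% vs 36% |
| half | 0.2-0.5 points | about 40-45% vs 36% |

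Hand check of the half-uptake row. Let D be the one-year gap between week-26 non-responders and responders. If all switch, the bias is 0.64 D. If half switch, the remaining group is 0.36 + 0.32 = 0.68 of the arm, and 0.32/0.68 = 0.47 of it are non-responders, so the bias is (0.64 - 0.47) D = 0.17 D. The ratio is 0.17/0.64 = 0.26, and 0.7 to 1.8 points become about 0.2 to 0.5.

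In the same model, week-26 non-responders improve by 0.4-0.9 points by one year with no treatment effect. That is the regression to the mean to which an uncontrolled before-after result in the extension is exposed, before any expectation effect.

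**3. As-randomised comparison**

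A separate model was used: baseline mean 7, SD 1.5; mean placebo fall 1; persistent SD 1.5; visit noise SD 1.3; about 26% placebo responders, hence 74% non-responders. Switchers are taken to be 26 weeks past BTA at week 52. A BTA effect of 1.0 is 0.95 after bounding the scale.

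As-randomised difference = effect in the BTA arm at 52 weeks - uptake × 0.74 × effect in switchers.

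- Sustained effect, 50% uptake: 0.95 - 0.5 × 0.74 × 0.95 = 0.60.
- 80% uptake: 0.95 - 0.8 × 0.74 × 0.95 = 0.39.
- Full uptake: 0.95 - 0.74 × 0.95 = 0.25.

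Simulation gives the same values. For other cases (positive favours BTA):

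| BTA effect at 26 / 52 weeks | Comparison | 50% uptake | 80% | 100% |
|---|---|---|---|---|
| 0 / 0 | as randomised | 0.0 | 0.0 | 0.0 |
| 0 / 0 | vs non-switchers | -0.36 | -0.89 | -1.73 |
| 1.0 / 1.0 | as randomised | 0.60 | 0.39 | 0.25 |
| 1.0 / 1.0 | vs non-switchers | 0.60 | 0.06 | -0.79 |
| 1.0 / 0.5 | as randomised | 0.12 | -0.09 | -0.23 |

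The as-randomised contrast stays at zero when BTA does nothing, provided the open-label injection has no expectation effect. It is diluted when the effect lasts. If the effect wanes, older BTA injections are set against newer ones and the contrast can fall slightly below zero.

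**4. The two statements on further injections**

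"Deblinding of subjects who did not meet the primary endpoint and offer them a second injection with BTA" covers all deblinded non-responders. "Participants who received placebo injection were offered to participate in our open label extension study" covers placebo recipients. Under the first, some women randomised to BTA would have had two injections by one year; under the second, none would. Even the group most naturally reported as one year after BTA is therefore undefined.

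**The case against.** The strongest reply is that the SAP does not plan the biased analyses. No section plans a comparison with non-switchers or a pooled before-after analysis. The stated rule is intention to treat, under which switchers stay in the placebo arm, and their 26-week extension questionnaires supply data near week 52. The aim is timed from BTA injection, Figure 2 is captioned as follow-up after the RCT has ended, and the outcome tables stop at 26 weeks. On that reading, efficacy means only persistence of response.

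Much of this stands. A reader might infer that the one-year data cannot show anything about efficacy, or that no between-arm p-value may be given after week 26. The document does not support that: an as-randomised contrast is a legitimate treatment-policy comparison, diluted and partly unblinded but not void. A reader might also infer that placebo non-responders are all moved to BTA, or that only they are unblinded. The text says they are offered BTA, and it deblinds non-responders in both arms. That responders stay blinded is an inference too; the SAP does not say when they are told.

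What the reply does not remove is the word efficacy in the aim, beside an extension aim that omits it, with nothing to say which of these readings will be reported. If persistence is meant, the SAP should say so.

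**Conclusion.** The point holds in this form: as planned, no unbiased BTA-versus-placebo effect of the first injection at one year can be obtained, so the aim should not be called efficacy without qualification. Under assumed inputs and no true effect, restricting placebo to non-switchers favours placebo by about 0.2-0.5 points at half uptake and 0.7-1.8 at full uptake. A sustained effect of 0.95 shrinks as randomised to 0.60 at half uptake and 0.25 at full uptake. The direction of these distortions follows from the design; their size depends on uptake, placebo response and within-woman correlation, none of which the SAP gives. Response by VAS alone is a further simplification, and the SAP joins VAS and PGI-I by *and* under Endpoints but by *or* under Randomization procedure and blinding, which alters who is deblinded.

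The figures do not show that the SAP plans a reversed comparison; they show what an unspecified efficacy aim leaves open.

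**What to change.** 1. Restate the one-year aim as safety and descriptive persistence of response.
2. Report all women randomised to BTA as one group, whatever their week-26 response, showing any further injection.
3. Report the open-label extension separately, on its own clock, and do not pool it with the BTA arm.
4. List placebo-arm one-year data by week-26 response and crossover.
5. If an as-randomised one-year contrast is given, label it a treatment-policy comparison diluted by switching and partly unblinded, not evidence of BTA efficacy versus placebo.
6. Reconcile the two statements on who is offered a further BTA injection, since they decide whether the BTA arm is also altered at one year.

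The cost is SAP wording and table shells. The offer of open-label BTA to placebo recipients and the 26-week analysis need not change. The sponsor gives up an unqualified claim of efficacy at one year.

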**Table 3. Primary outcomes.**

| Outcomes | BTA | Placebo | p-value |
| --- | --- | --- | --- |
| **Pain score** | N=xx | N=xx |  |
| Baseline | Mean (95% CI) | Mean (95% CI) |  |
| 4 weeks follow-up  8 weeks follow-up  12 weeks follow-up  26 weeks follow-up  BTA vs placebo*  Primary endpoint: 33% reduction in pain score, No. (%) | Mean (95% CI) Mean (95% CI) Mean (95% CI) Mean (95% CI)  NNN% | Mean (95% CI)  Mean (95% CI)  Mean (95% CI)  Mean (95% CI)  NNN% | X  X |
| **PGI-I** | N=xx | N=xx |  |
| 4 weeks follow-up  8 weeks follow-up  12 weeks follow-up  26 weeks follow-up  BTA vs placebo*  Primary endpoint: PGI-I 1 or 2, No. (%) | Mean (95% CI)  Mean (95% CI)  Mean (95% CI)  Mean (95% CI)  NNN% | Mean (95% CI)  Mean (95% CI)  Mean (95% CI)  Mean (95% CI)  NNN% | X  X |
| Data are presented as mean [95% CI] unless stated otherwise  *Pain score: average pain score last 4 weeks, scale 0-10.  **Based on linear mixed models including all time points except for baseline. Controlling for pain score (average past 4 weeks) at baseline and age at baseline.  *** p value for interaction | | | |

- 1. Secondary outcomes

| Outcome | Baseline n=xx | 26 weeks  n=xx | p-value |
| --- | --- | --- | --- |
| **PainDETECT total score** ^a^ |  |  |  |
| BTA  Placebo  *Botox vs. placebo | Mean (95% CI)  Mean (95% CI) | Mean (95% CI)  Mean (95% CI) | X |
| **Current VAS score^b^** |  |  |  |
| BTA  Placebo  *Botox vs. placebo | Mean (95% CI)  Mean (95% CI) | Mean (95% CI)  Mean (95% CI) |  |
| **EQ5D VAS score^c^** |  |  |  |
| BTA  Placebo  *Botox vs. placebo | Mean (95% CI)  Mean (95% CI) | Mean (95% CI)  Mean (95% CI) | X |
| **HADS depression scale^d^** |  |  |  |
| BTA  Placebo  *Botox vs. placebo | Mean (95% CI)  Mean (95% CI) | Mean (95% CI)  Mean (95% CI) | X |
| **HADS anxiety scale^d^** |  |  |  |
| BTA  Placebo  *Botox vs. placebo | Mean (95% CI)  Mean (95% CI) | Mean (95% CI)  Mean (95% CI) | X |
| **Pain catastrophizing scale (PCS)^e^** |  |  |  |
| BTA  Placebo  *Botox vs. placebo | Mean (95% CI)  Mean (95% CI) | Mean (95% CI)  Mean (95% CI) | X |
| **PFIQ-7 total score^f^** |  |  |  |
| BTA  Placebo  *Botox vs. placebo | Mean (95% CI)  Mean (95% CI) | Mean (95% CI)  Mean (95% CI) | X |
| **PFDI-20 total score^g^** |  |  |  |
| BTA  Placebo  *Botox vs. placebo | Mean (95% CI)  Mean (95% CI) | Mean (95% CI)  Mean (95% CI) | X |
| **PISQ-IR total score^h^** |  |  |  |

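### The SAP defines its primary endpoint with 'and', restates it with 'or', analyses two separate primary endpoints, and never says which test decides the trial

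*SAP*

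**What the plan says.** All of the following is current text of the SAP.

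- **Section 3, Primary endpoints** (plural heading): a VAS decrease "with 33% and a patient global impression of improvement score (PGI-I) of 1 or 2 (better or much better) at 26 weeks after injection". The two criteria are joined by *and*.
- **Section 4, Randomization procedure and blinding:** "Participants who did not meet the primary endpoint (33% reduction VAS score or PGI-I 1 or 2) were deblinded after 26 weeks". The parenthesis joins them by *or*. Section 3 also makes failure to reach the primary endpoint the entry condition for the open-label extension.
- **Section 5, Sample-size:** 94 women were required "to detect a statistical significant 33% difference in pain scores between the intervention group and the control group", with 80% power at two-sided 0.05.
- **Section 7, null hypothesis:** "there is no significant difference in decrease of chronic pelvic pain scores 26 weeks after treatment between the intervention group". PGI-I is not mentioned.
- **Section 7, analysis:** two items carry the primary label. The VAS item is "Primary endpoint: Percentage difference in VAS score between baseline and 26 weeks post-treatment will be calculated for each group". The PGI-I item is "Primary endpoint: the primary outcome of PGI-I scores being 1 or 2", compared between groups.
- **Section 13, Table 3:** one row is "Primary endpoint: 33% reduction in pain score, No" and another is "Primary endpoint: PGI-I 1 or 2, No", each a count with a percentage. No row counts women who met both.

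Section 11 leaves the reported effect open between a relative risk and a mean difference.

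**The concern.** The endpoint that Section 3 defines is never tested. In Table 3 a woman who meets one criterion counts in one row and not in the other, and two marginal counts cannot show how many women met both. If Section 3 is read instead as listing two endpoints, it agrees with Section 7 and Table 3. There is then no rule for the case where they disagree: no requirement that both succeed, no hierarchy and no split of alpha. Even the VAS item takes two forms, so choosing VAS would not by itself fix the test.

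What is at stake is the conclusion when VAS and PGI-I point different ways. From the SAP alone, whether PGI-I can rescue or sink the trial could be settled after the results are known. The *and*/*or* conflict also leaves it unclear which women were deblinded and offered the extension.

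**Working it through.** **1. The plan's own figure.** The SAP gives no SD, baseline mean, baseline correlation or response rate, so 94 can be neither reproduced nor refuted. Solved backwards, 47 per arm at 80% power and two-sided 0.05 detects a standardized difference of (1.960 + 0.842) × √(2/47) = 0.578 without covariate adjustment. At an assumed baseline correlation of 0.5 this becomes 0.578 × √(1 − 0.25) = 0.50. If the 33% were instead an absolute difference in responder proportions, control rates of 10–50% would need 27–35 per arm (33–41 with continuity correction), which is not 47. This fits the text of Section 5: the trial was sized on pain scores.

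**2. How many women the connective affects.** Assumptions: both criteria have the same response rate p, and the underlying scores are bivariate normal with correlation r. The proportion meeting exactly one criterion is 2 × (p − P(both)).

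| p | r | Exactly one | Of 94 | Of 47 on placebo |
|---|---|---|---|---|
| 20% | 0.4 | 24.8% | 23 | 12 |
| 20% | 0.8 | 14.2% | 13 | 7 |
| 30% | 0.4 | 31.6% | 30 | 15 |
| 30% | 0.8 | 17.8% | 17 | 8 |
| 40% | 0.4 | 35.6% | 33 | 17 |
| 40% | 0.8 | 19.8% | 19 | 9 |

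These women fail under *and* and succeed under *or*. Only the placebo group feeds the extension.

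**3. False-positive rate under each possible success rule.** Each test is at two-sided 0.05 with no true effect.

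- Either item suffices, independent tests: 1 − 0.95² = 9.75%.
- Either item suffices, two correlated normal score tests: 9.3% (r = 0.4), 8.8% (0.6), 7.8% (0.8).
- Either item suffices, pooled z-tests of proportions, 47 per arm, p = 20–40%, r = 0.4–0.8, simulated: 8.4–10.0%.
- Both items required, same simulation: 0.4–1.2%.
- VAS only, but free to choose between the score and the 33% count: 7.5–8.6%.

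**4. Power at the effect the trial was sized on.** A shift of about 0.58 SD moves a 20% placebo response to Φ(−0.842 + 0.578) ≈ 40%.

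| Confirmatory test | 20% vs 40% | Shift 0.58, placebo rate 20–40% |
|---|---|---|
| VAS score | about 80% | about 80% |
| Combined responder | 54% | about 53–68% |
| Both items significant | 37–42% | about 36–47% |

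At 20% vs 48% the combined responder reaches 81–82% and both-significant 71–74%. That scenario is a shift of 0.79 SD, where the VAS score would already have about 97% power, so it says little about the effect the trial was sized for.

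**The case against.** The best reply is that the lead measure can be inferred. The objective in Section 2, the aim stated in Section 6, the sample size and the only null hypothesis all name pain, and a PGI-I result cannot reject a null about pain scores. This stands, and it is why the VAS score is the natural choice. It does not close the gap: Section 7 and Table 3 still call PGI-I of 1 or 2 primary, nothing demotes it, and the VAS item itself has two forms.

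A reader might infer from the *or* in Section 4 that the trial succeeds if either item is significant, and so that its type I error is 8–10%. The document does not support this. That sentence classifies individual women for deblinding and is not a rule for trial success. No section states an either-item rule, although none excludes it.

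The deblinding sentence can also be read loosely as failing one criterion or the other, which would agree with Section 3. Because the parenthesis spells out the endpoint that was not met, its plain sense is *or*, and the SAP does not settle the matter.

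Finally, the published protocol may define the endpoint more clearly. Section 10 lists departures from it, and the endpoint is not among them. That tempers the worry about a choice made after the results, but it does not remove a conflict inside the SAP.

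**Conclusion.** The point holds as an internal contradiction with no stated decision rule. Followed as written, the plan never tests the endpoint in Section 3, and it leaves two primary items without saying which decides. The false-positive rate of about 8–10% is conditional on an either-item rule that the SAP does not state. The figures of 13–33 women and the power ranges rest on assumed response rates of 20–40%, latent correlations of 0.4–0.8 and equal rates for the two criteria, because the SAP gives none of these.

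Two stronger conclusions should not be drawn. The 26-week measurements are not biased by the ambiguity, since deblinding comes after them. And the sample size is not shown to be wrong; it cannot be checked from what is given.

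**What to change.** Before the primary analysis, name one confirmatory test.

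- **Preferred:** the between-arm difference in VAS score at 26 weeks from the mixed model, two-sided 0.05. This matches the null hypothesis and the measure used for the sample size.
- Label PGI-I of 1 or 2, the 33% VAS count and a combined flag (both criteria met) as secondary. Add the combined flag as a row in Table 3.
- Use the same VAS measure as primary in Section 7 and Table 3.
- If the sponsor keeps the combined responder of Section 3, or co-primary endpoints that must both be significant at 0.05, restate the power. At the effect detectable with 80% power on the score, these give about 53–68% and 36–47%.
- Correct the parenthesis in Section 4 to the chosen individual definition. Record which rule was actually applied at deblinding, so that the extension population is described accurately.

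The cost of the preferred option is SAP wording and one table row, with no new data. PGI-I loses its primary label.
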